### Consent, confidentiality and data storage

Group 1 patients will be sent the study patient information leaflet, along with the study questionnaire and a pre-paid envelope, to return the completed questionnaire to the research team.

When group 2 patients are invited for the consultation in the anticoagulation clinic, they will be sent the study patient information and asked to read it prior to their clinic visit. At the clinic visit, the pharmacist in clinic will ask the patient if they wish to participate in the study and address any questions they may have. For those patients who indicate that they interested, the pharmacist will recruit them into the study. Informed written consent will be taken by the pharmacist. For those patients who do not wish to participate, the pharmacist will still offer the patient the opportunity to switch to a NOAC, as per local guidance.

A similar process to that of group 2 patients will be followed for group 3 patients, at the appropriate time for study III.

All recruited patients will be reviewed in Haematology outpatients at the respective hospitals, by pharmacists trained in the study.

Data collected for the purposes of the study will be recorded by the pharmacist on a pre-determined study form, which captures the information required for the study. At the earliest opportunity, the principal researcher associated with the study will transfer the data to an excel database at the respective hospitals and subsequently transfer to an SPSS database, with the hard copy of the data collection form being filed and stored in a locked office within the haematology department at King’s College Hospital, with only members of the clinical team having access to this office.

One week after entry of a patient’s data onto the SPSS database, the data which had been entered will be re-checked for any entry discrepancies by the principal researcher.

As soon as a patient consents to participate in the study, they will be given a unique study number. This number will be entered onto the SPSS database and will only be traceable back to an individual patient by accessing the study form for the patient in the haematology department at King’s College Hospital.

All electronic data will be encrypted and password protected.

Only direct members of the research team will have access to the full set of electronic data generated within the study. The completed questionnaires for studies I, II and III will be stored within a locked office within the haematology department at King’s College Hospital.

### Sample size and statistical analysis

#### Study I & II

Patients who are >75 % in TTR (group 1) will be classified as adherent and those who are <50 % in TTR (group 2) will be classified as non-adherent. To determine if patients’ beliefs about warfarin and their illness perception is associated with their adherence status, univariate analyses will first be conducted to identify the key variables that will be entered into the multiple logistic regression model. Assuming a recruitment ratio of 1:1 of non-adherent : adherent patients, a total sample size of 180 to 240 patients will be able to accommodate 6 to 8 predictive variables. i.e. up to 120 patients who are adherent and up to 120 patients who are non-adherent are required as measured by TTR.

Multiple linear regression will be used to examine whether illness and treatment beliefs can predict adherence to NOAC. Using the formula that 15 observations are needed per degree of freedom, a sample size of 240 will be able to test whether illness and treatment beliefs (11 dimensions) and up to five demographic/clinical variables can predict adherence to NOAC. Therefore a sample size of 240 patients who are switched to NOAC is required.

However, as the refusal rate for switching to NOAC for eligible patients is not known, and given that the NOAC patient sample will derive from those who are non-adherent to warfarin (<50 % TTR), at least 240 patients – rather than 120 patients - who are non-adherent will need to be recruited in order to be able to perform both the linear regression analysis and logistic regression analysis. A conservative refusal rate of 30 % would suggest 342 patients who are <50 % TTR on warfarin would need to be recruited into group 2.

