The Switching study is a series of prospective studies designed to investigate the association between medication adherence and patients’ beliefs about anticoagulation therapy (warfarin and subsequently NOAC) together with beliefs about their illness and anticoagulation-related quality of life.

The Switching study aims to test the following hypotheses:*Patients’ beliefs about warfarin and their illness perceptions is associated with their adherence to warfarin as measured by time in treatment range (TTR), over and above any clinical or demographic variables.**Patients’ beliefs about NOAC at baseline and their illness perception can predict their adherence to NOAC, over and above any clinical or demographic variables.**Patients with symptomatic disease (either VTE or AF) have higher necessity scores for anticoagulant treatment compared to patients with asymptomatic disease.**Patients with a TTR >75 % have low concerns and higher necessity scores for warfarin than those with a TTR <50 %.**Patient’s responses to the illness perception questionnaire (IPQ) is specific to treatment and will change, following a switch to NOAC.**Patient’s quality of life scores improve following a switch to NOAC.*

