## Abbreviations

ACTS, anti-clot treatment scale; BMQ, beliefs about medication questionnaire; CHA_2_DS_2_VASc, congestive heart failure, hypertension, age ≥75 years (2), stroke (2), vascular disease, age 65–74 years, sex category (female (1)); CHADS_2_, congestive heart failure, hypertension, age ≥75 years, stroke (2); CrCl, creatinine clearance; DVT, deep vein thrombosis; FBC, full blood count; GP, general practitioner; HASBLED, hypertension, abnormal renal or liver function, stroke, bleeding, labile INRs, elderly, drugs or alcohol; INR, International Normalised Ratio; IPQ, illness perceptions questionnaire; MRCI, medication related complexity index; NOAC, novel oral anticoagulant; PTS, post-thrombotic syndrome; SAMe-TT_2_R_2_, sex (female), age (<60 years), medical history, treatment (interacting drugs), T (tobacco use within 2 years (2)), race (non-white (2)); TTR, time in therapeutic range; UEs, urea and electrolytes; VKA, Vitamin K antagonists

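### Univariate screening in Study I does not secure the adjustment that hypothesis 1 requires, and the 180 to 240 sample size counts only the variables that survive the screen

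*Protocol article*

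**What the plan says.** Hypothesis 1, at the end of the Background, states that patients' beliefs about warfarin together with their illness perceptions "is associated with their adherence to warfarin as measured by time in treatment range (TTR), over and above any clinical or demographic variables".

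Under Sample size and statistical analysis (Study I & II), adherence is the TTR group: above 75% (group 1) against below 50% (group 2). Predictors are chosen as follows: "univariate analyses will first be conducted to identify the key variables that will be entered into the multiple logistic regression model". The section names no clinical or demographic variable that stays in the model whatever its univariate result.

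The size is set by the number of variables in the final model: "a total sample size of 180 to 240 patients will be able to accommodate 6 to 8 predictive variables", with 1:1 recruitment, so that "up to 120 patients who are adherent and up to 120 patients who are non-adherent are required".

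The Study II linear model in the same section is handled differently. "Using the formula that 15 observations are needed per degree of freedom", it allows 240 patients to test whether "illness and treatment beliefs (11 dimensions) and up to five demographic/clinical variables can predict adherence to NOAC". No screening step is mentioned there.

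**The concern.** Hypothesis 1 concerns a set of variables (beliefs and illness perceptions) conditional on another set (clinical and demographic). The selection rule does not follow that structure, and three problems result.

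- **Adjustment.** A confounder with a modest marginal difference between the TTR groups is dropped by chance, so the set adjusted for depends on the sample.
- **Inference after selection.** A belief scale reaches the final model because it already looked extreme in these data. Its p-value there, and any joint test of the scales that survived, no longer has its nominal meaning.
- **Sample size.** If only survivors are counted, the model looks adequately supported when the data have in fact been used to search a longer list.

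The article says that the data from studies I and II will be used to design the clinical pathway evaluated in Study III, so beliefs singled out in this way could shape the intervention.

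**Working it through.** **1. Reproduce the plan's figure.** With 1:1 groups the smaller outcome group is N/2. 180/2 = 90 and 90/6 = 15; 240/2 = 120 and 120/8 = 15. Both ends fit 15 per variable exactly. A rule of 10 would give 2 × 10 × 6 = 120 and 2 × 10 × 8 = 160, which does not fit. The figure of 15 is therefore inferred for Study I; the article states it only for the Study II linear model, where 15 × (11 + 5) = 240.

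**2. Count candidates as Study II does.** Study I gives no candidate count, so I borrow the 16 terms of Study II (11 dimensions plus up to five covariates).

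- 90/16 = 5.6 and 120/16 = 7.5 per candidate.
- For the 11 dimensions alone: 90/11 = 8.2 and 120/11 = 10.9.
- Fifteen per candidate would need 15 × 16 = 240 per group, 480 in total.

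Group 2 is raised to 342 for Study II, but no group 1 figure above 120 is given, so the smaller group stays at 120 or fewer.

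**3. Chance that a real covariate difference is screened out.** Assume a true difference of 0.2 SD and a normal approximation.

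- At 120 per group, SE = √(2/120) = 0.129 and z = 0.2/0.129 = 1.55. The covariate is dropped with probability 66% at a threshold of p<0.05 and 39% at p<0.20.
- At 90 per group, SE = √(2/90) = 0.149 and z = 1.34. The probabilities are 73% and 47%.
- Five independent covariates of this kind at 120 per group are all kept with probability 0.34^5 = 0.5% to 0.61^5 = 8%.

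**4. Simulation.** Assumptions: 120 against 120; 11 belief scales with no effect given the covariates; five covariates; correlation 0 or 0.3; covariate shift 0 or 0.2 SD; final tests at 5%; 1000 runs per setting. The article gives neither the threshold nor alpha, so both are assumptions. Results in %, for screening thresholds 0.05 / 0.10 / 0.20:

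| Correlation, shift | Joint test of surviving beliefs rejects | Unscreened 11-df block test rejects | All five covariates kept |
|---|---|---|---|
| 0, 0 | 43.4 / 49.6 / 49.8 | 7.0 / 7.0 / 7.0 | not relevant (no true shift) |
| 0, 0.2 SD | 38.3 / 47.4 / 47.1 | 7.6 / 7.6 / 5.4 | 0.6 / 2.3 / 8.8 |
| 0.3, 0 | 30.1 / 23.5 / 27.4 | 6.7 / 7.2 / 6.8 | not relevant (no true shift) |
| 0.3, 0.2 SD | 17.4 / 11.9 / 7.9 | 7.4 / 7.9 / 6.6 | 3.8 / 9.5 / 19.7 |

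At 120 against 342 with threshold 0.10, the joint test of survivors rejects in 6.3% to 49.6% and the block test in 4.1% to 6.6%.

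**5. Error rates that are not raised (120 against 120).**

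- Unconditional error per belief coefficient: 1.3% to 5.0% with screening, 5.2% to 6.0% in the full 16-term model.
- At least one falsely significant belief: 13.8% to 42.8% with screening, 42.2% to 49.4% in the full model. For 11 independent tests, 1 − 0.95^11 = 43%.

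**6. Error given that a belief passed the screen.** Of the null beliefs that passed, the share then significant is 16% to 90% where covariates do not differ, 24% to 78% where they differ but are uncorrelated with beliefs, and 4% to 8% where they differ and are correlated.

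**The case against.** The strongest reply is that screening does not produce more false belief findings overall. Step 5 bears this out: neither the error per coefficient nor the chance of any false belief is higher than in the full model. The article also plans no joint test of survivors, and the inflation of such a test nearly disappears in some settings (7.9% in the mildest at 120 against 120). A reader might infer that the procedure generally inflates false positives; that is not supported. What remains is narrower: p-values read on the selected variables are not nominal, and no valid single test of hypothesis 1 can be built from the survivors.

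A reader might also infer that the plan cannot test beliefs beyond clinical variables at all. That goes too far. The model is multivariable and adjusts for every covariate that passes. The defect is that adjustment is left to chance.

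A full protocol or SAP may fix the threshold, and its absence from an article is no fault. But the screening rule itself is stated here, and the loss of covariates occurs at every threshold tried.

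Finally, a reader might suspect circularity through HAS-BLED, whose definition includes labile INRs. The documents do not support this as a Study I problem: Table 1 schedules that score for studies II and III, and nothing names it as a Study I candidate.

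**Conclusion.** The point holds in limited form and should be corrected. The stated selection rule does not secure the adjustment written into hypothesis 1: with five covariates each shifted by 0.2 SD, all five were kept in 1% to 20% of simulated studies. Inference after selection is not nominal: a joint test of surviving null beliefs rejects in about 6% to 50%, against about 5% to 8% for a pre-specified block test. The sample size counts 6 to 8 retained variables, while the same section counts all 16 terms for Study II; on that count Study I has 5.6 to 7.5 per candidate.

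These sizes rest on assumed thresholds of 0.05 to 0.20, a 5% final test, correlations of 0 or 0.3, a candidate list borrowed from Study II, and an inferred rule of 15 per variable. The conflict between the rule and the hypothesis depends on none of them.

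**What to change.** 1. Delete the univariate step.
2. Force a short pre-specified clinical and demographic set into the logistic model, for example age, sex, ethnicity and indication.
3. Add all belief and illness dimensions as one block, and make a single likelihood-ratio test of that block the test of hypothesis 1.
4. Report individual odds ratios from penalised estimation (Firth or ridge), as description rather than as separate tests.
5. Restate the size: 180 to 240 patients support 6 to 8 terms in total at 15 per variable, candidates included.

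The block model goes beyond 6 to 8 terms. With four single-parameter covariates and 11 dimensions it has 120/15 = 8 per term at best. That is why hypothesis 1 should rest on the block test, which stayed close to its nominal level in the simulation with 16 terms at this size, and why the individual coefficients need penalisation. No extra patients are needed for this. If 15 per term were wanted for all 16 terms, group 1 would have to rise from 120 to 240; the planned group 2 of 342 already exceeds that.

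The costs are wider intervals for individual odds ratios, and the chosen covariates must be available for group 1. Those patients are approached only by post, so the items would have to come from clinic records if they are not already held.

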#### Study III

Three hundred forty-two patients will be recruited into group 2 which will act as the control group. Power calculations (GPower 3.1) assuming one-tailed analysis using an independent groups design, suggest that a 1:1 matching i.e. recruiting 342 patients into the intervention group (group 3) would allow for the detection of a small-sized effect of the intervention (d = 0.20).

The Switching study has been reviewed and given a favorable opinion by the London-Dulwich Research Ethics Committee: REC reference: 13/LO/1468.

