#### Study III

Following completion of studies I and II, the data collected will be analysed and used to design a clinical pathway which will be evaluated in a third (independent) group of patients (group 3 – patients with a TTR <50 %). The clinical pathway will be informed from the 2-month follow-up data collected up to visit 3 from patients in group 2 of study II. Group 3 patients will have the same follow-up in clinic as per the schedule outlined for group 2 patients, and analysis for study III will also be conducted on an intention to treat basis. The findings from group 2 patients (beliefs about medicines, illness perceptions, quality of life and adherence to anticoagulant therapy) will then be compared to the findings from group 3 patients. In this way, this controlled study design will then allow an assessment of the effectiveness of the clinical pathway developed. Figure 1 summarises the three studies which form this programme of work.

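### Study III bases its power for d = 0.20 on 342 recruited per group, but at the protocol's own 30% refusal only about 239 per group would have the NOAC outcomes it compares

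*Protocol article*

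**What the plan says.** All references are to the protocol article.

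- **Sample size, Study I & II.** The regression of NOAC adherence on beliefs needs 240 switched patients: "Therefore a sample size of 240 patients who are switched to NOAC is required". The section says the refusal rate is unknown, adopts "A conservative refusal rate of 30" per cent, and arrives at 342 to be recruited into group 2.
- **Sample size, Study III.** "Three hundred forty-two patients will be recruited into group 2 which will act as the control group". The calculation is described as "assuming one-tailed analysis using an independent groups design", and the claim, at a 1:1 ratio and d = 0.20, is that "recruiting 342 patients into the intervention group (group 3) would allow for the detection of a small-sized effect". Neither alpha nor power is given.
- **Switching study series, Study III.** Groups 2 and 3 are compared on beliefs, illness perceptions, quality of life and adherence, and "analysis for study III will also be conducted on an intention to treat basis".
- **Study outcomes and Table 1.** Every listed outcome is timed from the switch or concerns NOAC therapy. Visits 2 to 4 are scheduled by time on NOAC.
- **Study II, on decliners.** Patients who decline are followed, but only clinically relevant outcomes and reasons for declining are named. No follow-up questionnaires are scheduled for them.

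**The concern.** The same number carries two meanings in adjacent sections. Under Study I & II, 342 is the number to recruit so that about 240 remain after refusal. Under Study III, 342 per group is the number that delivers the stated sensitivity, with no allowance for refusal. Patients who stay on warfarin cannot supply a NOAC pill count, NOAC coverage or beliefs about the NOAC, and the pathway under evaluation exists to support patients on NOACs.

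Study III is the programme's only evaluation of that pathway. If the stated sensitivity is higher than the design provides, a null comparison will carry less information about small effects than a reader of the article would suppose.

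**Working it through.** **Inputs**

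- Recruited per group: 342, ratio 1:1 (Sample size, Study III).
- Standardised difference: d = 0.20; one-tailed; independent groups (same section).
- Refusal: 30%, stated for group 2 (Sample size, Study I & II). Its use for group 3 is an assumption, based on the same TTR <50% criterion and the same visit schedule.
- Alpha: not stated. 0.05 one-tailed is assumed, with 0.025 as the range.
- Power target: not stated. 80% is a benchmark only.

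**Where 342 comes from**

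240 / 0.70 = 342.9, and back again 342 × 0.70 = 239.4. So 342 recruited corresponds to about 239 switchers.

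**Formula**

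Power = Φ(d × √[n₁n₂/(n₁+n₂)] − z), with z = 1.645. For equal groups the root is √(n/2).

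**The plan's own statement**

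n = 342: 0.20 × √171 = 2.615; 2.615 − 1.645 = 0.970; power 83.4% (noncentral t: 83.4%). For 80% power 310 per group suffice, so the statement is correct if all 342 per group are analysable and unaffected by refusal.

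**With refusal applied, d = 0.20**

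| Refusal | n per group | d × root | minus 1.645 | Power |
|---|---|---|---|---|
| 0% | 342 | 2.615 | 0.970 | 83% |
| 10% | 308 | 2.482 | 0.837 | 80% |
| 20% | 274 | 2.341 | 0.696 | 76% |
| 30% | 239 | 2.186 | 0.541 | 71% |
| 30% in group 2 only | 239 v 342 | 2.372 | 0.727 | 77% |

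The noncentral t gives 70.5% at 239 per group, so the normal approximation is adequate.

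**If intention to treat keeps all 342**

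Suppose decliners are measured, the pathway does nothing for them, and the standard deviation is unchanged. The average effect is then 0.70 × 0.20 = 0.14. 0.14 × √171 = 1.831; 1.831 − 1.645 = 0.186; power 57%.

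**Detectable d at 80% power**

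d = (1.645 + 0.842) × √(2/n), one-tailed.

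- n = 342: 0.19.
- n = 240: 2.487 × 0.0913 = 0.227.
- n = 240 with a two-sided 5% test: (1.960 + 0.842) × 0.0913 = 0.256.

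**Sensitivity to alpha**

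At one-tailed 0.025, power for d = 0.20 is 74% with 342 per group and 59% with 239.

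**The case against.** The other side has several fair points.

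- *The printed calculation is right.* With 342 per group a one-tailed test does detect d = 0.20 with good power. This stands: the fault is which number was entered, not the arithmetic. Since no alpha or power is declared, no declared power is missed.
- *The 30% is a cautious planning value, given for group 2 only.* This stands, and is why a range is shown. At 10% refusal power is still about 80%.
- *Decliners are enrolled and followed, and illness perception and ACTS are not NOAC-specific.* True: they consent and complete baseline questionnaires before being asked to switch, so 342 should not be read as a list of people merely approached. The full protocol might collect these two instruments from decliners. NOAC adherence and beliefs about the NOAC remain impossible for them, and including them on the other scales leads to the diluted case, which is worse.
- *Powering on switchers sits badly with intention to treat.* Agreed. Switching is chosen after recruitment, so the analysis set must be settled, not assumed.

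A reader might also infer that the one-tailed test is an error and that true power is 59% (two-sided, 239 per group). The article openly plans a one-tailed test, so that figure judges the design by a test it does not use. A reader might likewise infer that Study II cannot support its planned model terms. That needs an assumed loss to follow-up; without one, 239 against the required 240 is rounding, and a condensed article may leave attrition to the full protocol.

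**Conclusion.** The point holds as an inconsistency between two adjacent sections. Study III uses recruited patients as though all were analysable, one section after 342 was built to absorb refusal.

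At the protocol's own 30%, power for d = 0.20 is about 71% if both groups refuse at that rate, 77% if only group 2 does, and 57% if everyone is analysed with a diluted effect. Each is below the 83% that 342 per group implies. These figures rest on one-tailed alpha 0.05, on group 3 refusing at group 2's rate where both refuse, and, for the 57%, on decliners gaining nothing from the pathway. The size depends on the refusal actually met: at 10% the shortfall is about 3 percentage points.

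The documents do not show that a declared power is missed, that a two-sided test is required, or that Study II is undersized.

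**What to change.** In the Study III sample-size section:

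1. State alpha and power.
2. State the analysis set for each compared outcome (switchers or all recruited) and reconcile it with the intention-to-treat statement in the Study III design section.
3. If the set is switchers, restate the detectable effect on that number: about d = 0.23 at 80% power, one-tailed alpha 0.05, with about 240 per group, before any loss by the 1-year visit. If a two-sided test is chosen, the figure is 0.26.
4. If all recruited patients are analysed, say how decliners' outcomes will be obtained and state the diluted effect (0.14 for a true 0.20 among switchers at 30% refusal) with its power.
5. Say what refusal rate is assumed for group 3.

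Moving to a two-sided test is optional. The cost is wording and a slightly less favourable stated sensitivity; no further patients are needed.
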